### 3.6. Exposure

The exposure of interest is RSV vaccination during pregnancy. The vaccine data could be obtained from pharmacy dispensing records, general practice records, immunisation registers, vaccination records, medical records or other databanks. We will consider a single administration of one dose between 24–36 weeks of gestation. An woman is considered exposed from the date of vaccination until the end of pregnancy for all pregnancy and birth outcomes.

### 3.7. Outcomes

The proposed key outcomes of interest, along with their respective outcome-specific exposure windows, are described in Table 2 and encompass preterm birth, time between vaccination and birth, stillbirth, hypertensive disorders of pregnancy, Guillain-Barré Syndrome (GBS), low birth weight (LBW), and small for gestational age (SGA). The outcome time between vaccination and birth holds more statistical power than preterm birth, as preterm birth is a categorical outcome while the time between vaccination and birth is continuous [21,22]. Distinguishing between outcomes measured during pregnancy and those assessed at or after birth is crucial, as it affects statistical analysis and interpretation.

Additional outcomes for maternal immunisation may be added based on the risk profile of the vaccine [30]. The clinical definitions for outcomes of interest should be based on either the Global Alignment on Immunization Safety Assessment (GAIA), Brighton Collaboration, or the official World Health Organization (WHO) definitions [31,32]. While these definitions can be adjusted, utilising these official, globally recognised definitions will enhance harmonisation and study comparability. The outcomes should be ascertained using algorithms based on codes for diagnoses, procedures, medical products and information from each specific databank. We recommend working with each data source to understand how information can be retrieved and how outcomes and other variables are coded.

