### 3.9. Study Size

All women meeting eligibility criteria during the study observation period should be included in the study. It is currently unknown how many women will receive RSV vaccination during pregnancy, as the National Immunisation Technical Advisory Groups need to determine whether this will be included in routine maternal immunisation programs in the country or region where the study is conducted. Minimal detectable risks can be calculated based on the assumption that every vaccinated pregnant individual could be compared with N unvaccinated pregnant individual(s) (1:N ratio). The desired alpha level is 5%, and risk ratio (RR) values of 1.5, 2.0, 2.5, and 4.0 may be considered (Supplementary Table S2). For pregnancy and birth outcomes, the required number of exposed women to achieve a power of 80% under different RR values may assume prevalence rates in the unexposed group ranging from 0.2% to 6.0%. To detect an RR of 1.5 with 95% confidence interval (CI) for preterm birth, approximately 1200 pregnancies ending in live birth would need to be included in a data source. For rare outcomes during pregnancy such as GBS, we calculated the power obtainable assuming a maximum sample size of 30,000 exposed pregnant women, with an incidence rate of 1/100,000 person-years in the comparator group [39].

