#### 3.10.2. Measures of Effect

Primary analyses should estimate counts, proportions, and risk or rate ratios with 95% CI for events occurring and measurable during pregnancy, and counts, proportions, and prevalence ratios with 95% CI for outcomes measurable at birth. Comparison of outcomes by exposure status should be conducted using multivariable generalised linear models. These analyses should control for potential confounding by matching. Balance of covariates should be analysed using standardised mean differences (SMDs), some characteristics and risk factors for the exposure or outcomes may remain unbalanced, which should be analysed using plots of SMDs. To address this, propensity score methods can be employed and propensity scores can be adjusted or additionally matched on if necessary [40]. To obtain more power for the analysis of preterm birth, we recommend that time from vaccination to birth should be analysed separately [21,22].

The primary analyses may face-selective censoring due to treatment crossover in the comparator cohort, necessitating the use of inverse probability censoring weights. To maintain statistical power, unexposed pregnant women in the matched comparator cohort should be censored upon treatment violation, while exposed pregnant women should not be censored. Weights can be used to correct for the bias introduced by such censoring, ensuring more accurate and reliable results. Additionally, a sensitivity analysis can be conducted to explore the effect of censoring the matched pair if treatment crossover happens in the previously unexposed pregnant woman. Another sensitivity analysis may be carried out to explore the effect of exclusion of medically indicated iatrogenic births.

For subgroup analyses, secondary analyses can be conducted among immunocompromised or high-risk pregnancies and stratified by weeks of gestation at the time of vaccination.

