Because of safety concerns, the primary outcome measure under examination is preterm birth, considering the varying recommendations by EMA, FDA and MHRA regarding the optimal gestational age for vaccination [5,6,7,12,13]. Notably, concerns over preterm births have led to the suspension of a phase 3 trial for another candidate RSV prefusion subunit vaccine [10]. However, a significant challenge in analysing preterm birth in observational studies lies in its direct relationship with gestational age at the time of vaccination. For instance, administering the vaccine at 35 weeks of gestation cannot result in an preterm birth of less than 35 weeks. Therefore, we emphasise the critical importance of matching participants based on gestational age at the time of vaccination. In fact, participants will be enrolled in a sequence of weekly trials based on their gestational age at the time of vaccination. Additionally, we have added the outcome time between vaccination and birth. This outcome holds more statistical power than preterm birth, as preterm birth is a categorical outcome while time between vaccination and birth is continuous. Also, this approach allows us to examine the median time between vaccination and preterm births, which is crucial for identifying specific underlying mechanisms. For instance, it can reveal whether preterm infants are born days, weeks, or months after vaccination. Moreover, this outcome is independent of the accuracy of gestational age assessment [21,22]. Other outcomes can be chosen, and we refer to the GAIA initiative, which defined more than 20 outcomes relevant to maternal immunisation [31].

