**Birth outcomes**			
Low birth weight (LBW) [28]	Low birth weight is defined by the WHO as a weight at birth of less than 2500 g, regardless of gestational age.	Pregnancies ending with live births	From birth until one month after birth
Small for gestational age (SGA) [29]	Small for gestational age is defined by the WHO as a birth weight below the 10th percentile for gestational age and sex. SGA can be caused by placental dysfunction, referred to as foetal growth restriction (FGR), or it can be due to a constitutionally small foetus without any pathological causes. Other possible causes include congenital malformations or infections.	Pregnancies ending with live births	From birth until one month after birth

**Table 3 vaccines-13-00272-t003:** Covariates of interest.

Covariate	Definition
Gestational age at time of vaccination	Gestational age at time of vaccination is defined as the time between the last menstrual period (LMP) and the date of vaccination, measured in weeks.
Calendar time at time of vaccination	Calendar time at the time of vaccination is defined as the specific calendar date of the vaccination, expressed in weeks (e.g., week 48 of the year 2024 or week 12 of the year 2025).
Maternal age	Maternal age at time of vaccination is defined as the age of the pregnant person at the date of vaccination. This age is determined by subtracting the individual’s date of birth from the date of vaccination.

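### The power and dating-independence claims for time from vaccination to birth hold only under conditions that the protocol does not state

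*Protocol article*

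**What the plan says.** Section 3.7 ranks the two outcomes on the ground that one is continuous and the other is not: "The outcome time between vaccination and birth holds more statistical power than preterm birth, as preterm birth is a categorical outcome". The Discussion repeats this. Section 3.10.2 turns it into a recommendation for the preterm question itself: "To obtain more power for the analysis of preterm birth, we recommend that time from vaccination to birth should be analysed separately". The Discussion, which names preterm birth as the primary outcome measure, adds of time to birth: "Moreover, this outcome is independent of the accuracy of gestational age assessment".

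The sizing in Section 3.9 concerns preterm birth: "The desired alpha level is 5%, and risk ratio (RR) values of 1.5, 2.0, 2.5, and 4.0 may be considered", with the number needed to "achieve a power of 80% under different RR values" and "prevalence rates in the unexposed group ranging from 0.2% to 6.0"%. Its figure for preterm birth reads: "To detect an RR of 1.5 with 95% confidence interval (CI) for preterm birth, approximately 1200 pregnancies ending in live birth would need". No effect in days, standard deviation or test is given for the continuous outcome.

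Section 3.1 and Table 1 match each unexposed woman on the same week of gestation and the same calendar week. Table 3 counts gestational age at vaccination from the LMP to "the date of vaccination, measured in weeks".

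**The concern.** A continuous outcome gains power over its dichotomised form when the whole distribution moves. The safety question here is whether there are extra early births. If the excess lies in the preterm tail only, a few births per hundred move by weeks and the rest do not move, so the mean changes little and the median hardly at all. The reason given, continuous against categorical, does not settle which outcome is more powerful.

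The independence statement also needs a limit. An unexposed woman has no vaccination date, and gestational-age matching places the start of her interval.

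At stake is interpretation. Anyone who takes the ranking from this template could read a null time-to-birth result as the stronger test and as reassurance on preterm birth, when it may be the weaker one. A dating difference between the groups could also produce or hide a difference in days without being suspected.

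**Working it through.** **1. The protocol's own figure.** Inputs from Section 3.9: RR 1.5, 80% power, 5% alpha (two-sided assumed) and 6.0% unexposed risk, the top of the stated range. Exposed risk is 1.5 × 6% = 9%. With 1:1 matching and pooled variance:

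n = [1.96·√(2·0.075·0.925) + 0.842·√(0.09·0.91 + 0.06·0.94)]² / 0.03² = 1,209 per arm.

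This reproduces the stated 1,200 as the exposed arm. Power at 1,200 per arm is 79.7%.

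**2. The same excess, confined to births before 37 weeks.** The documents do not give birth timing. Assumed: term births with SD 8–10 days, preterm births with SD 15 days, and a mean gap between term and preterm births of 20–50 days.

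- Mean shift = 0.03 × gap = 0.6 to 1.5 days.
- Variance in one arm = (1−p)·SD_term² + p·SD_preterm² + p(1−p)·gap² + 49/12, the last term for entry day within the week.
- Example: gap 30 days, term SD 8. Variance is 128.5 at p = 0.06 and 156.3 at p = 0.09, so the pooled SD is 11.9. Shift 0.90; SE = 11.9·√(2/1200) = 0.487; power = Φ(0.90/0.487 − 1.96) = 46%. For 80% power, n = 2·(1.96+0.84)²·142.4/0.90² ≈ 2,760 per arm.

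Over the whole grid, power for means is 23–64%, and 1,766 to 6,154 per arm are needed for 80%.

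Simulation with 1,200 per arm, excess confined to preterm births and entry day uniform within the matched week:

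| Analysis | Power |
|---|---|
| Preterm yes/no | 77–81% |
| Mean time to birth | 43–57% |
| Rank test | 22–26% |
| Log-rank | 10–14% |

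The median moved by about 0.4 day. Further simulations with other preterm-timing distributions gave 47–59% for means and 23–27% for the rank test. A rank test with follow-up ended at 37w0d kept 78–82%.

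Outer bounds for means at 1,209 per arm:
- SD 14, gap 21 days: shift 0.63, SE 0.569, power 20%.
- SD 10, gap 35 days: shift 1.05, SE 0.407, power 73%. This corner is barely coherent, since a 35-day gap alone contributes 0.06·0.94·35² ≈ 69 of the variance of 100.

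**3. The opposite mechanism.** If all births shift, moving a normal distribution from 6% to 9% below the cut takes z(0.09) − z(0.06) = 0.214 SD. Then n = 2·(1.96+0.84)²/0.214² ≈ 343 per arm, against 1,209. In simulation, moving every birth 4–5 days earlier (preterm 8.6–9.8%) gave about 100% power for time to birth and 69–94% for preterm birth.

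**4. Dating.** In a vaccinated woman the interval needs only two recorded dates. The comparator's start comes from the gestational-week match.

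- Systematic difference of 1 day between groups, no true effect, 1,200 per arm: 1/(SD·√(2/1200)) = 2.23 at SD 11 and 1.75 at SD 14. The test rejects in about 61% and 42% of studies, in place of 5%.
- Random mismatch within the week: a uniform day from 0 to 6 has variance 4, so the pair difference has SD √8 = 2.8 days. Its mean is zero. Set against a variance of 100–196 (SD 10–14), it adds 4/196 to 4/100, or about 2–4%.
- Error with the same distribution in both groups cancels in the mean difference.

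**The case against.** The strongest reply is that the protocol's ranking is correct under a plausible mechanism, and nobody knows which mechanism applies. That stands. A reader might infer that time to birth is simply the inferior outcome and that the claim should be reversed or deleted. Step 3 shows that the documents do not support this.

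Second, preterm birth remains the primary measure and the basis of sizing, time to birth is to be analysed separately, and nothing lets a null result on one override the other. That also stands: the misreading is a risk that the wording invites, not a rule in the protocol. With the 30,000 exposed women that Section 3.9 assumes for GBS, either analysis would be well powered: at 1:1, even the SD 14, 21-day case exceeds 99.9%. The ranking matters for smaller sources, the subgroups and the separate gestational-week trials that Section 3.1 recommends.

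Third, the birth-timing inputs and the tests are this review's assumptions, and an analysis plan may choose others. This is true. The direction held in every scenario with a confined excess; the size of the loss varied widely.

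Fourth, the independence sentence may refer only to the interval as Table 2 defines it. In that sense it is right for vaccinated women. A reader might go further and infer that same-week matching itself biases the result, most of all at week 36, where few days of preterm risk remain. That would need a systematic imbalance between groups, and nothing in the documents shows one.

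**Conclusion.** Both claims are too broad as worded. If the sizing effect (RR 1.5 on 6%, about 1,200 per arm at 1:1) acts only on births before 37 weeks, power is about 80% for preterm yes/no, about 45–60% for mean time to birth (20–73% under wider assumptions) and about 25% for a rank test. If all births shift earlier, the protocol's ranking is right. The ordering therefore depends on the mechanism, not on whether the outcome is continuous.

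Independence from dating accuracy belongs to the measured interval in vaccinated women. The group comparison relies on comparable dating: a systematic one-day difference is about as large as the effect sought, while shared error causes no bias and random within-week mismatch costs little. The calculations rest on an assumed birth-timing distribution, a two-sided 5% test and 1:1 matching.

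**What to change.** - In Sections 3.7 and 3.10.2 and the Discussion, say that time to birth has more power if vaccination shifts most births earlier, and may have less if the excess is confined to preterm births. State that a null time-to-birth result is not stronger evidence than the preterm result.
- In the Discussion, limit the independence statement to the interval measured in vaccinated women, and say that the comparison relies on comparable dating in the two groups.
- Beside preterm risk, analyse time to birth with follow-up ended at 37w0d. Keep unrestricted time to birth as supportive.
- Adjust for gestational age at time zero in days where the source supports it.

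The cost is some rewording and slightly more analysis. The 37w0d cut-off itself depends on dating, as preterm birth already does, and day-level gestational age may be imprecise in sources that estimate pregnancy start by algorithm.

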### 3.8. Covariates

Crucial covariates of interest include matching variables: gestational age, calendar time, maternal age, immunocompromised status and high-risk pregnancy, for which definitions are provided in Table 3. Similar to outcomes, we recommend covariates to be identified using diagnoses, procedures, medical products and information from each specific databank. Additionally, variables associated with the outcomes and exposure of interest should be included [33,34,35,36,37,38]. An example is presented in Supplementary Table S1. Maternal vaccinations such as influenza, SARS-CoV-2, Tetanus, Diphtheria and Pertussis (Tdap) given prior to RSV vaccination should also be recorded, as well as RSV monoclonal antibodies and RSV vaccination of the offspring.

### 3.9. Study Size

All women meeting eligibility criteria during the study observation period should be included in the study. It is currently unknown how many women will receive RSV vaccination during pregnancy, as the National Immunisation Technical Advisory Groups need to determine whether this will be included in routine maternal immunisation programs in the country or region where the study is conducted. Minimal detectable risks can be calculated based on the assumption that every vaccinated pregnant individual could be compared with N unvaccinated pregnant individual(s) (1:N ratio). The desired alpha level is 5%, and risk ratio (RR) values of 1.5, 2.0, 2.5, and 4.0 may be considered (Supplementary Table S2). For pregnancy and birth outcomes, the required number of exposed women to achieve a power of 80% under different RR values may assume prevalence rates in the unexposed group ranging from 0.2% to 6.0%. To detect an RR of 1.5 with 95% confidence interval (CI) for preterm birth, approximately 1200 pregnancies ending in live birth would need to be included in a data source. For rare outcomes during pregnancy such as GBS, we calculated the power obtainable assuming a maximum sample size of 30,000 exposed pregnant women, with an incidence rate of 1/100,000 person-years in the comparator group [39].

### 3.10. Data Analysis

Detailed methodology for summary and statistical analyses should be documented in a statistical analysis plan and be drafted prior to any analyses. Any major modifications to the prespecified analyses should be clearly reported. Changes should be annotated and amended when they are major.

#### 3.10.1. Baseline Characteristics

Baseline characteristics for both maternal RSV-exposed and pregnant comparator cohorts should be reported as means, standard deviations, medians and other quartiles for continuous variables, and counts and proportions for categorical variables. Any missing baseline characteristics and the duration of the look-back period should be explicitly described. To assess the comparability of matched cohorts, a standardised difference between the index and comparator cohort can be computed for each baseline characteristic. In cases where categorical variables have more than two levels, an overall standardised difference should be calculated.

#### 3.10.2. Measures of Effect

Primary analyses should estimate counts, proportions, and risk or rate ratios with 95% CI for events occurring and measurable during pregnancy, and counts, proportions, and prevalence ratios with 95% CI for outcomes measurable at birth. Comparison of outcomes by exposure status should be conducted using multivariable generalised linear models. These analyses should control for potential confounding by matching. Balance of covariates should be analysed using standardised mean differences (SMDs), some characteristics and risk factors for the exposure or outcomes may remain unbalanced, which should be analysed using plots of SMDs. To address this, propensity score methods can be employed and propensity scores can be adjusted or additionally matched on if necessary [40]. To obtain more power for the analysis of preterm birth, we recommend that time from vaccination to birth should be analysed separately [21,22].

The primary analyses may face-selective censoring due to treatment crossover in the comparator cohort, necessitating the use of inverse probability censoring weights. To maintain statistical power, unexposed pregnant women in the matched comparator cohort should be censored upon treatment violation, while exposed pregnant women should not be censored. Weights can be used to correct for the bias introduced by such censoring, ensuring more accurate and reliable results. Additionally, a sensitivity analysis can be conducted to explore the effect of censoring the matched pair if treatment crossover happens in the previously unexposed pregnant woman. Another sensitivity analysis may be carried out to explore the effect of exclusion of medically indicated iatrogenic births.

For subgroup analyses, secondary analyses can be conducted among immunocompromised or high-risk pregnancies and stratified by weeks of gestation at the time of vaccination.

#### 3.10.3. Meta-Analysis

In case multiple data sources are utilised, we recommend employing a common analytics tool, such as R studio, to conduct the analyses separately within each data source consistently. Subsequently, utilising the main estimates obtained from each data source, appropriate random-effects meta-analytic methods should be applied to derive a combined effect estimate [41,42]. To assess potential heterogeneity across data sources, it is advisable to visually inspect and check using forest plots, displaying the study site estimates and a pooled estimate with 95% CIs. In situations where there are zero events, we suggest pooling incidence rates, as they can be zero and still yield valid standard errors.

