**Maternal outcomes**			
Hypertensives disorders of pregnancy [25,26]	Hypertensives disorders of pregnancy include: Gestational hypertension (defined as systolic blood pressure greater than or equal to 140 mm/Hg and/or diastolic blood pressure greater than or equal to 90 mm/Hg arising de novo at ≥20 weeks’ gestation in the absence of proteinuria or other findings suggestive of pre-eclampsia) Preeclampsia de novo (defined as gestational hypertension accompanied by one or more of the following new-onset conditions at ≥20 weeks’ gestation: (a) Proteinuria (b) Other maternal end-organ dysfunction, including neurological complications, pulmonary oedema, haematological complications, renal insufficiency, or impaired liver function (c) Uteroplacental dysfunction Preeclampsia superimposed on chronic hypertension (among persons with chronic hypertension, development of new proteinuria, another maternal organ dysfunction(s), or evidence of uteroplacental dysfunction HELLP (Haemolysis, Elevated Liver Enzyme, Low Platelet) is a serious manifestation of pre-eclampsia and should be assessed if available.	Pregnancies ending with live and non-live births	From time of vaccination to end of pregnancy
Guillain-Barré Syndrome (GBS) [27]	GBS is defined as an neurological condition in which a person’s immune system attacks the peripheral nerves. It is a rare condition and the cause of it is not fully understood. Most cases follow an infection with a virus or bacteria, e.g., Campylobacter jejuni, cytomegalovirus, Epstein-Barr virus and the Zika virus. In rare instances, vaccinations may increase the risk of people getting GBS.	Pregnancies ending with live and non-live births	From time of vaccination until 42 days following vaccination

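### The zero-event pooling rule rests on a standard-error property that fails for raw and log rates, and on the protocol's own figures zero exposed cases is the expected GBS result

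*Protocol article*

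**What the plan says.** Section 3.10.3 (Meta-Analysis) applies "In case multiple data sources are utilised". Each source is analysed separately, and then "appropriate random-effects meta-analytic methods should be applied to derive a combined effect estimate". For sparse outcomes it adds one rule with a reason attached: "In situations where there are zero events, we suggest pooling incidence rates, as they can be zero and still yield valid standard errors". It names no scale, transformation, count model or interval method, and does not say how pooled rates would be contrasted between vaccinated and comparator women.

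Three other places bear on how often the rule would be used:

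- Section 3.9 (Study Size), on GBS: "we calculated the power obtainable assuming a maximum sample size of 30,000 exposed pregnant women". The comparator rate assumed there is 1 per 100,000 person-years. The same section says that "risk ratio (RR) values of 1.5, 2.0, 2.5, and 4.0 may be considered".
- Table 2, GBS row, sets the risk window: "From time of vaccination until 42 days following vaccination".
- Section 3.10.2 makes risk or rate ratios with 95% confidence intervals the primary measure for events during pregnancy, with confounding controlled by matching.

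**The concern.** The sentence does more than leave a detail open. It gives a reason for the rule, and on the scales most analysts would reach for first the reason is wrong. This article is a template meant to be adapted by others, so the error may be carried into their plans.

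Two things are at stake. An analyst who pools raw or log rates from zero-event sources gets either a failed computation or a rate of zero with no apparent uncertainty. The second can be misread as firm reassurance on GBS, which Section 1 names as a safety event of interest. Also, a pooled rate is not the between-arm ratio of Section 3.10.2. If each arm's rates are pooled across sources separately and then compared, the within-source matched comparison is lost.

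**Working it through.** **Inputs**

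| Input | Value | Source |
|---|---|---|
| Exposed women, maximum assumed for GBS | 30,000 | Section 3.9 |
| Comparator GBS rate | 1 per 100,000 person-years | Section 3.9 |
| GBS risk window | 42 days | Table 2 |
| Largest risk ratio listed | 4.0 | Section 3.9 |
| Matching ratio 1:N | N not fixed; 1, 4 and 10 tried | assumption |
| Number of sources | not fixed; 3 to 8 of equal size tried | assumption |

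The text shown prints no expected GBS count and no GBS power, so there is no figure of the plan's own to reproduce.

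**1. Standard error at zero events.** Take x events in T person-years, with x Poisson.

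- Raw rate x/T: SE = √x / T. At x = 0 this is 0.
- Log rate: SE = 1/√x. At x = 0 this is undefined, as is the log rate itself.
- Square-root rate: SE = √(1/(4T)). This does not depend on x. For T = 3,449.7 it is 0.0085, which is finite. The Freeman-Tukey variance is finite too.

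The claimed property is therefore false on the first two scales and true on the third.

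**2. What this does to pooling.** Suppose four equal sources of 862.4 person-years have 0, 0, 0 and 1 events. With inverse-variance weights on the raw scale, the three zero-event sources get infinite weight and the source with the case gets 862.4² ≈ 743,773. No pooled estimate can be formed. Adding a between-source variance does not cure this, because the zero-event sources are still treated as having no sampling error. On the square-root scale the pooled rate is 7.2 per 100,000 person-years (95% CI 0 to 63.5). The crude pooled rate is 1/3,449.7 = 29.0 per 100,000. Even among methods that run, the choice of scale changes the answer.

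**3. How often GBS meets the rule.**

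- Exposed person-time: 30,000 × 42/365.25 = 3,449.7 person-years. This assumes that every woman completes the window, so it is a maximum.
- Expected exposed cases, no effect: 3,449.7 × 0.00001 = 0.0345. P(none) = exp(−0.0345) = 96.6%.
- At a risk ratio of 4.0: 0.0345 × 4 = 0.138. P(none) = exp(−0.138) = 87.1%.
- Split over 3 to 8 equal sources, no effect: 0.0115 to 0.0043 expected per source. P(none) is 98.9% to 99.6% in each.
- Both arms, no effect, same window: expected total is 0.0345 × (1 + N). P(no case in either arm) is 93.3% at 1:1, 84.2% at 1:4 and 68.4% at 1:10.
- Sensitivity: a full year of person-time per exposed woman would still give only 30,000 × 0.00001 = 0.3 expected cases, with P(none) = 74.1%.

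**4. What zero cases would show.** The exact two-sided 95% upper limit is 3.689/T, where 3.689 is half the 97.5% point of chi-squared on 2 degrees of freedom. 3.689/3,449.7 = 106.9 per 100,000 person-years, about 107 times the assumed background.

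**The case against.** The strongest reply is that the sentence is under-specified rather than false. Square-root and Freeman-Tukey scales give finite variances at zero, and Poisson mixed models and exact limits handle zeros. Section 3.10.3 asks only for appropriate random-effects methods, and Section 3.10 leaves detailed methodology to a statistical analysis plan. This stands in part: a reader might infer that a zero rate can never have a valid standard error, or that the section prescribes inverse-variance weights, and the document supports neither. But the sentence credits the property to incidence rates as such and omits the condition that makes it true. Leaving the method to a later plan does not correct a wrong reason given here.

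A second reply is that the rule is a suggestion, limited to multi-source studies, for one rare outcome in a generic protocol whose Discussion names preterm birth as primary. That is fair. A reader might infer that pooled rates become the main GBS analysis. The document does not say so, since ratios remain primary in Section 3.10.2. The counts show only that in a multi-source study the ratio would often not be estimable, so that the fallback would usually be what is left. The 0.0345 is also for the exposed arm alone; comparators add cases, and how many depends on N.

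A third tempting inference is that the protocol states a GBS power that is wrong. It does not. Section 3.9 says that obtainable power was calculated, but the text prints no result, and Supplementary Table S2 is not among the documents at hand. It may already report low power.

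**Conclusion.** The point holds in limited form. The reason given for the zero-event rule is incorrect for raw and log rates, and the text names no scale or model under which it would be correct. On the protocol's own inputs the consequence is not remote for GBS: 0.0345 expected exposed cases, and a 97% chance of none (87% at a risk ratio of 4.0). These figures assume Poisson counts, complete 42-day follow-up, and the stated 30,000 women and background rate. The per-source figures also assume equal source sizes, and the both-arm figures an assumed N. The conclusion applies only to multi-source studies and does not affect the preterm birth analysis. It is a defect of wording and method specification, not of design.

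**What to change.** Replace the last sentence of Section 3.10.3 with text along these lines:

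> Where one or more sources have no events, source-by-arm event counts and person-time will be analysed jointly in a Poisson model with a log person-time offset, stratified by source, with exact or profile-likelihood confidence limits, so that the exposed-comparator contrast is made within source. Where no event occurs in either arm, the ratio is not estimable; the outcome will be reported descriptively as observed versus expected counts with exact Poisson limits.

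A named variance-stabilising scale would also make the standard error finite, but the four-source example shows that its result can sit far from the crude rate, and it does not by itself supply the between-arm contrast.

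The descriptive fallback is needed because the count model does not rescue the ratio when both arms are empty, which has probability 93% at 1:1 and 84% at 1:4 under no effect. It would help to state for GBS what a zero count could exclude: with 3,450 exposed person-years, only rates above about 107 per 100,000 person-years.

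Cost: no change to design or data collection. Sources must share counts and person-time by arm rather than estimates alone, which departs from the separate-analysis scheme for sparse outcomes. The pooled count model also lacks the covariate adjustment and censoring weights of Section 3.10.2 unless these are carried into it, and the report should say so.
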